### Assessment

Participants will be assessed 4 times: at baseline, 6 months (end of therapy), 12 months (6 months after end of therapy) and 18 months (1 year after end of therapy). Assessments will be conducted on all participants including those who do not complete treatment.

The timing of administration of assessment measures is shown in Table 3.Measures administered only at baseline:1.1.A self-report questionnaire will be used to assess sociodemographic and clinical variables (age, gender, race, occupation, marital status, education, eating disorder onset and lifetime history of eating disorders) and will include a specific questionnaire to determine income status, namely the ‘Critério de Classificação Econômica Brasil 2014’ [30].1.2.Mini International Neuropsychiatric Interview (MINI). The MINI is a reliable and valid structured interview for psychiatric diagnoses according to the DSM [2]. Only the MINI-5 [31] for DSM-IV [32] is translated into Portuguese. Thus, the MINI-5 will be used in this study, with modifications to the coding of all disorders to accord with DSM-5 diagnoses as in the MINI-7 [33].Measures repeated from baseline to 12-month follow-up:2.1.Anthropometry will include waist and hip circumferences (mean of 3 measures), pulse and sitting blood pressure. Height and weight will be measured with a stadiometer and calibrated scale, from which BMI (kg/m^2^) will be calculated.2.2.Eating disorder psychopathology instruments:2.2.1.Eating Disorder Examination Edition 17.0D [34]: the EDE is the ‘gold standard’ semi-structured interview used to assess eating disorder symptoms and diagnoses. Four subscales can be derived measuring severity of dietary restraint, eating, shape and weight over concern. These are averaged for a global score. Version 16.0 [18] of the EDE was translated to Brazilian/Portuguese by collaborators from the Federal University of Rio de Janeiro ([name] and [name]), by authors of this paper (MAP, AC) and by a PROATA eating disorder specialist ([name] – CM), back-translated to English by a certified translator and the final version approved by one of the authors of EDE ([name]). The reliability and concurrent validity of the translated EDE was tested and found to be satisfactory. There was 80 % inter-interviewer agreement (kappa 0.69) on the diagnosis made with the EDE interview and 77.3 % agreement (kappa 0.68) (unpublished data provided by author AC). The diagnosis was made according to the eating disorder module of the Structured Clinical Interview for DSM-IV Axis I Disorders-Patient Edition (SCID-I/P) interview [35] (Portuguese version) [36]. Small adjustments were made by the author MAP, so that the Portuguese version used in the study is now consistent with the 17th version of the EDE [34], in order to derive DSM-5 diagnoses.2.2.2.Eating Disorder Examination Questionnaire (EDE-Q) [37]: a self-report measure is derived from the EDE interview. Like the EDE, it has four subscales (dietary restraint, eating, weight and shape concerns). An unpublished Brazilian/Portuguese translation of the more recent 28-item version of the EDE-Q (V. 6.0) [18] was prepared by CM and MAP, and this version will be used. This translation utilised the validated European Portuguese version of the original 36-item EDE-Q [38], which was then modified to be consistent with Brazilian/Portuguese.2.2.3.Loss of Control over Eating Scale (LOCES) [39]: a 24-item self-report that examines the presence of loss of control during the binge eating episodes in the last 4 weeks. A Brazilian/Portuguese translation and assessment of psychometric properties (factor analysis and convergent validity) has been completed ([name] et al., manuscript submitted).2.2.4.Binge Eating Scale (BES) [40]: a 16-item self-report instrument that has been translated and validated in a Brazilian sample [41]. This scale evaluates the presence and severity of binge eating. It has adequate psychometric properties in the Brazilian version, with a cut-off point of 17 for the screening of eating disorders in obese individuals seeking treatment for weight loss.2.3.General psychopathology instrument:2.3.1.Depression, Anxiety and Stress Scale (DASS-21) [42, 43] in a translated and validated Brazilian/Portuguese version [44]. This self-report instrument measures the presence and severity of depressive symptoms, anxiety and stress.2.4.Adaptive function:2.4.1.Health-related quality of life will be measured with the 12-item Short Form Health Survey (SF-12) [45]. This is a self-report questionnaire that measures health-related quality of life, subdivided in 2 scales – Physical Health Component Summary scales (PCS) and Mental Health Component Summary scales (MCS). A score lower than 30 on the MCS indicates severe impairment in mental health, and a score from 31 to 40 indicates moderate impairment. This is a widely-used measure with sound psychometric properties and has been translated into Brazilian/Portuguese [46].2.4.2.Disability will be assessed using a question analogous to the ‘days out of role’ questions employed in the Australian National Survey of Mental Health and Well-Being [47]. Participants will be asked to record the number of days after the following question: *During the past 4 weeks, on how many days, if any, were you unable to complete your work, study or household responsibilities because of any problem with your (physical or emotional) health?* This was translated by the author MAP.Measures only at baseline and end-of-treatment.The following medical pathology tests will be performed at baseline and end-of-treatment only: fasting circulating glucose, insulin, lipid profile, liver function test, electrolytes, urea, creatinine and uric acid.Measures at end-of-treatment only.4.1.Client/patient satisfaction questionnaire [48]. This eight-item scale assesses general satisfaction with services. It has a high internal consistency (*α* = 0.93) and correlates with therapist’s assessment of client satisfaction and with early treatment drop out. This was translated by the author MAP.4.2.Participants will be asked which group, experimental or control, they thought they were in. When all participants have completed 12-month follow-up and data has been processed, participants will be debriefed, and full information will be provided about HAPIFED and CBT-E.

**Table 3 Tab3:** Time schedule for the randomised controlled trial

Semesters	2015 Jan/Jun	2015 Jul/Dec	2016 Jan/Jun	2016 Jul/Dec	2017 Jan/Jun	2017 Jul/Dec	2018 Jan/Jun	2018 Jul/Dec
Stages								
HAPIFED and CBT-E groups 1 and 2 Recruitment and intervention	x	x						
HAPIFED and CBT-E groups 3 and 4 Recruitment and intervention		x	x					
HAPIFED and CBT-E groups 5 and 6 Recruitment and intervention			x	x				
HAPIFED and CBT-E groups 7 and 8 Recruitment and intervention			x	x				
HAPIFED and CBT-E groups 9 and 10 Recruitment and intervention				x	x			
HAPIFED and CBT-E groups 1 and 2 Follow-up (6 and 12 months)			x	x				
HAPIFED and CBT-E groups 3 and 4 Follow-up (6 and 12 months)				x	x			
HAPIFED and CBT-E groups 5 and 6 Follow-up (6 and 12 months)					x	x		
HAPIFED and CBT-E groups 7 and 8 Follow-up (6 and 12 months)					x	x		
HAPIFED and CBT-E groups 9 and 10 Follow-up (6 and 12 months)						x	x	
Development and maintenance of the database		x	x	x	x	x	x	
Preparation and publication of results					x	x	x	x

*CBT-E* cognitive behavioural therapy–enhanced, *HAPIFED* Healthy APproach to WeIght management and Food in Eating Disorders

### Data collection, management and analysis

Researchers conducting outcome data entry will be blind to the study group of participants. Between-group outcome analyses will not begin until after the final 1-year follow-up. Governance of data and an independent Data Monitoring Committee (DMC) responsible for interim mid-point in recruitment safety and futility analyses of de-identified data will be conducted at the University of Western Sydney site. The DMC will be composed of a biostatistician with expertise in RCTs, and two senior independent clinical researchers with expertise in RCTs. The trial will be discontinued if assessed to be futile and/or participants’ binge eating is increasing significantly and/or attrition is over 50 %. Therapists under supervision who are not blind to treatment arm will be responsible for the safety of individual participants and will receive directly any concerns about an individual from the DMC.

STATA (StataCorp, College Station, TX, USA) for most statistics will be used. Baseline univariate between-group tests will be done to compare groups on outcome variables, clinical and demographic data. Data will be analysed following ‘intention-to-treat’ principles. Generalised estimating equations [49] with a logit response function will be used for dichotomous outcomes, such as achieving a 5 % reduction in body weight. Linear mixed effects modelling [50] will be used to test for between-group differences in the continuous outcome measures, namely weight loss, levels of ED symptom change, adaptive function, quality of life, depression and anxiety levels, waist circumference, blood pressure, and biochemical markers such as circulating lipid or glucose levels. Putative covariates will be diagnostic group (BN or BED) and use of psychotropic medication. Predictors of outcomes at 6-month and 12-month follow-up to be tested will include the rate of early (by mid-treatment) reduction in binge eating.

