Emotion regulation skills	Yes	Yes

*CBT* cognitive behavioural therapy, *CBT-E* cognitive behavioural therapy-enhanced, *ED* eating disorders, *HAPIFED* Healthy Approach to WeIght management and Food in Eating Disorders

The primary aim of this paper is to detail the protocol (version registered as at 11 July 2015) of a single-blind superiority RCT that compares HAPIFED with CBT-E in weight loss efficacy. A second aim will be to investigate the safety of the introduction of weight loss management particularly for people with BN, but also for those with BED who are overweight/obese.

The primary hypothesis of the RCT will be that at end-of-treatment, 6-month and 12-month follow-up, participants receiving HAPIFED will have lost more body weight than those receiving CBT-E. Secondary hypotheses will be that participants receiving HAPIFED compared to CBT-E group will have significantly improved indicators of weight management e.g., reduced body waist measurement, improved cardiovascular and metabolic status, and that participants in either group who achieve binge eating remission will achieve a greater degree of weight loss.

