## Method/Design

### Participants

This study will comprise 100 participants recruited from both community and clinics. Assessments and therapy will be conducted in the Eating Disorders Programme (PROATA) clinic in the Department of Psychiatry of the Federal University of São Paulo (UNIFESP), Brazil. The inclusion criteria are: age ≥ 18 years; either sex; a primary eating disorder diagnosis of BN or BED type according to the *Diagnostic and Statistical Manual of Mental Disorders, fifth edition* (DSM-5) and/or the proposed *International Classification of Diseases, eleventh version* (ICD-11) criteria [2, 3]; and a body mass index (BMI) ≥ 27 and < 40 kg/m^2^. The exclusion criteria are: a current diagnosis of psychosis or bipolar disorder and/or a high level of suicide risk; use of weight loss medication; history of bariatric surgery; clinical conditions that interfere with appetite regulation (e.g., Prader-Willi and Cushing syndromes); and currently receiving psychological treatment for eating disorders.

The present study *a priori* power analysis was based on the estimate of a moderate between group effect size (i.e., 0.6) in the primary outcome of weight loss. To achieve this with power of 0.8 and 1-tailed alpha *p* < 0.05, a minimum of 36 participants per group is required according to Cohen’s tables. Allowing for attrition the sample size is 50 per arm and 10 per therapy group.

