### Procedure

Recruitment will take place between June 2015 and December 2016. The recruitment will be through PROATA’s treatment waiting list, printed notices and broadcasting of written and oral media. The first contact will be made by the research team by phone or Email. Those who will be considered eligible for the study will be invited for a first interview at which point informed written consent will be completed, inclusion and exclusion criteria confirmed, and a medical history and physical examination including height and weight (with calibrated scale) undertaken. Medical assessment will accord with international guidelines for weight loss management. Laboratory tests will be circulating fasting lipid profile, fasting glucose matched with insulin, liver function, electrolytes, urea, uric acid and creatinine. A semi-structured interview and self-report questionnaires to determine the eating disorder and co-morbid diagnoses and suicide risk will be conducted. A second appointment will be scheduled for a semi-structured interview that confirms the eating disorder diagnosis and completes a detailed assessment of eating disorder symptoms and behaviours (as detailed in the study timeline on Table 2).

**Table 2 Tab2:** Timetable of administration of assessment measures

	Baseline	Mid-treatment	End-oftreatment	Follow-up (6 and 12 months)
Demographic questionnaire	✓			
Mini International Neuropsychiatric Interview	✓			
Anthropometry^a^	✓	✓	✓	✓
Eating Disorder Examination	✓		✓	✓
Eating Disorder Examination Questionnaire	✓	✓	✓	✓
Other self-report measures^b^	✓	✓	✓	✓
Adaptive function self-report measures^c^	✓		✓	✓
Physical state biomarkers^d^	✓		✓	
Client satisfaction and success of blinding questions			✓	✓

^a^Waist and hip circumferences, pulse and sitting blood pressure, height and weight for BMI calculation; BMI is also monitored weekly in session

^b^LOCES, BES, DASS21

^c^SF-12: ‘days out of role’

^d^Fasting blood glucose, insulin, lipid profile, liver function test, electrolytes, urea, creatinine and uric acid

*BES* Binge Eating Scale, *BMI* body mass index, *DASS-21* Depression, Anxiety and Stress Scale-21, *LOCES* Loss of Control Over Eating Scale, *SF-12* 12-item Short Form Health Survey

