### Outcomes

The primary outcome of this intervention will be a reduced body weight sustained to 12 months after completion of the intervention. Secondary outcomes will be (i) improved metabolic indicators of weight management; (ii) reduction in eating disorder symptoms, namely binge eating, loss of control over eating, driven exercise, purging, and self-induced vomiting and dysfunctional cognitions (weight and shape overvaluation and eating concerns); (iii) being less than 1 standard deviation above the community mean for global score on the Eating Disorder Examination (EDE) [18]; (iv) improved adaptive function (‘days out of role’), physical and mental health-related quality of life (HRQoL); and (v) reduced levels of depression and anxiety.

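### The covariates named for the linear mixed models omit the baseline value of each outcome, and the planned baseline significance tests are uninformative under randomisation; correcting both is a modest improvement at no cost

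*Protocol article*

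**What the plan says.** Under Data collection, management and analysis, the article sets out the model for continuous outcomes: "Linear mixed effects modelling [50] will be used to test for between-group differences in the continuous outcome measures, namely weight loss", followed by symptom, function, quality-of-life, mood, waist, blood-pressure and biochemical measures. It then names the adjustment variables: "Putative covariates will be diagnostic group (BN or BED) and use of psychotropic medication". No baseline outcome value is among them. Earlier in the same paragraph it says: "Baseline univariate between-group tests will be done to compare groups on outcome variables, clinical and demographic data".

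The baseline values are collected. In Table 2 (Procedure), anthropometry is taken at baseline and at every later assessment, and its footnote lists "Waist and hip circumferences, pulse and sitting blood pressure, height and weight for BMI calculation". The biomarkers are taken at baseline and end of treatment only.

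The primary outcome is worded as a change throughout. The hypothesis in Background is that "participants receiving HAPIFED will have lost more body weight than those receiving CBT-E". The power statement under Participants rests on an "estimate of a moderate between group effect size (i.e., 0.6) in the primary outcome of weight loss". Outcomes says "The primary outcome of this intervention will be a reduced body weight sustained to 12 months after completion of the intervention". The dichotomous example in the analysis section is "such as achieving a 5 % reduction in body weight". The article does not say whether baseline weight is subtracted, modelled as a repeated response, or used as a covariate.

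**The concern.** In a randomised trial the baseline value of a continuous outcome is usually a useful covariate. It reduces residual variance and corrects for whatever baseline imbalance chance has produced. Here the article names its covariates and leaves this one out, in a trial of 50 per arm where precision is limited.

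The baseline tests are a separate weakness. Participants are individually randomised with concealed allocation, so any baseline difference arises by chance, and a p-value tests a null hypothesis already known to be true. Such tests produce nominally significant differences that readers may take for a failure of randomisation.

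At stake are some precision, protection of the estimate against chance imbalance, and clear reporting. The validity of the primary comparison is not in question.

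**Working it through.** **The plan's own figure.** Inputs from Participants: standardised effect 0.6, power 0.8, one-tailed alpha 0.05. Normal approximation: n = 2 × (1.645 + 0.842)² / 0.6² = 34.35, so 35 per group. The exact t-test gives 35.04, so 36. The stated minimum of 36 per group reproduces and does not depend on baseline adjustment.

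**Precision for weight loss.** Let r be the correlation between baseline and follow-up weight, with equal standard deviations s. The article gives no r; 0.85 to 0.95 is assumed.

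- Variance of a change score: 2(1 − r)s².
- Residual variance after baseline adjustment: (1 − r²)s².
- Ratio, adjusted to change score: (1 + r)/2.

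The ratio is 0.925 at r = 0.85, 0.95 at r = 0.9 and 0.975 at r = 0.95, a reduction of 7.5%, 5% and 2.5%.

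In terms of power at the stated minimum of 36 per group (normal approximation, effect 0.6 on the change scale):

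| Analysis | Power | n per group for 80% |
|---|---|---|
| Change score alone | 0.816 | 35 |
| Baseline added, r = 0.9 | 0.833 | 33 |
| Baseline added, r = 0.95 | 0.825 | 34 |

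The gain is about 1 to 2 percentage points.

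**Bias.** In 4,000 simulated trials with 36 per arm, the mean estimate at r = 0.9 was −0.268 both with the baseline covariate and with the change score; the standard errors were 0.102 and 0.105. At r = 0.95 both means were −0.189, with standard errors 0.0740 and 0.0745. Both analyses centre on the same effect.

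**Chance imbalance.** If the arms differ at baseline by D, a change score leaves (1 − r)D in the estimate: 5% of D at r = 0.95 and 15% at r = 0.85. Take an imbalance of two standard errors with 36 per arm: 2 × √(2/36) = 0.47 s.

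- r = 0.95: 0.05 × 0.47 = 0.024 s. Divided by the standard deviation of change, √0.10 = 0.316 s, this is 0.07, or 12% of the planned 0.6.
- r = 0.85: 0.15 × 0.47 = 0.071 s. Divided by √0.30 = 0.548 s, this is 0.13, or 22% of the planned 0.6.

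This is an unfavourable draw, and the shift can go in either direction. Baseline adjustment removes it.

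**Other outcomes.** Against a change score, the reduction is 15% at r = 0.7 and 25% at r = 0.5. For an outcome analysed as a follow-up level without baseline, the ratio is 1 − r², a reduction of 49% at r = 0.7 and 25% at r = 0.5. These correlations are also assumptions.

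**Baseline tests.** With k independent tests at 5%, the chance of at least one nominally significant difference under correct randomisation is 1 − 0.95^k: 40% for k = 10, 64% for k = 20, 79% for k = 30. The article gives no count, and many of its measures are correlated, so this is only an illustration.

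**The case against.** The strongest reply is one of scope. This is a condensed article, and how baseline enters a mixed model is commonly settled in the full protocol or analysis plan. If baseline weight is one of the repeated responses, a separate covariate is not needed. Much of this stands, and it is why the point is small. It is not a complete answer: the article does name covariates and does commit to baseline tests, and both statements can be improved. A baseline response matches covariate adjustment only if the arm means are constrained equal at baseline; left free, with complete data, the treatment contrast is again the difference in change.

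Several stronger readings are tempting, and the documents do not support them.

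- *Baseline weight is the strongest predictor of the primary outcome.* That could fit follow-up weight, but the analysed outcome is weight loss. On that scale, with the assumed r, baseline explains only 2.5% to 7.5% of the variance.
- *Adjustment would cut variance by 72% to 90%.* This is r² for raw follow-up weight modelled with no baseline at all, an analysis of the primary outcome that the article does not describe.
- *Covariates will be chosen by baseline p-value.* The tentative label and the tests stand in the same paragraph, but the article states no such rule and names two covariates in advance.
- *On-trial medication will be adjusted for.* The wording sets no time limit, but nothing says use during treatment is meant, and Table 2 lists no repeated medication assessment.
- *Only 36 per arm are planned.* That is the required minimum; 50 per arm are to be randomised, and non-completers are also to be assessed.

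**Conclusion.** The point holds as a modest improvement that costs nothing. The named covariates omit the baseline value of the outcome, and the planned baseline significance tests serve no purpose in a randomised comparison.

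For weight loss as a change score, adding baseline weight is worth 2.5% to 7.5% of variance and removes the remaining 5% to 15% of any chance imbalance. Both figures rest on the assumed correlation of 0.85 to 0.95 and on equal standard deviations at the two times. The benefit is greater for outcomes with lower correlations or analysed as levels. There is no bias on average, and no number in the article is wrong. Dropping the baseline tests improves the reporting but changes no primary estimate.

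**What to change.** Amend the wording of Data collection, management and analysis, or the analysis plan, before between-group analyses begin:

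1. For each continuous outcome, include its baseline value as a covariate, or model it as a response with arm means constrained equal at baseline.
2. Replace the tentative covariate list with a fixed one: diagnostic group and psychotropic use, both as recorded at baseline.
3. Add the randomisation block. Allocation was restricted in blocks of 20, five blocks for 100 participants, and the analysis should reflect that restriction.
4. Replace the baseline tests with descriptive summaries by arm, without p-values.

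The cost is wording only. Baseline outcome values and block membership are already available, and psychotropic use need only be tied to its value at entry. Sample size, visits and treatment are unaffected. Five blocks use four degrees of freedom, which is minor with 100 participants.

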### Ethics and dissemination

The study has been approved by the Human Research Ethics Committee of the Federal University of São Paulo, Brazil (CAAE 43874315.4.0000.5505). Written informed consent including information on confidentiality provisions will be obtained from each subject. Only investigators and authorised research personnel will have access to the database. Reports will be made regularly to the committee including results of interim safety analyses by the DMC.

The trial results will be submitted to a peer-reviewed scientific paper, and authors will present results at appropriate scientific meetings and community and advocacy organisations, as well as being released to the media following publication.

The Standard Protocol Items: Recommendations for Interventional Trials (SPIRIT) Checklist for recommended items to address in a clinical trial protocol is found as an additional file (see Additional file 1).

